## Abstract

**Background:**

Glaucoma is a chronic eye disease associated with irreversible visual loss. In Africa, glaucoma patients often present late, with very advanced disease. One-off procedures, such as laser or surgery, are recommended in Africa because of lack of or poor adherence to medical treatment. However, acceptance of surgery is usually extremely low. To prevent blindness, adherence to treatment needs to improve, using acceptable, replicable and cost-effective interventions. After reviewing the literature and interviewing patients in Bauchi (Nigeria) motivational interviewing (MI) was selected as the intervention for this trial, with adaptation for glaucoma (MIG). MI is designed to strengthen personal motivation for, and commitment to a specific goal by eliciting and exploring a person’s reasons for change within an atmosphere of acceptance and compassion. The aim of this study is to assess whether MIG increases the uptake of laser or surgery amongst glaucoma patients where this is the recommended treatment. The hypothesis is that MIG increases the uptake of treatment. This will be the first trial of MI in Africa.

**Methods:**

This is a hospital based, single centre, randomized controlled trial of MIG plus an information sheet on glaucoma and its treatment (the latter being “standard care”) compared with standard care alone for glaucoma patients where the treatment recommended is surgery or laser.

Those eligible for the trial are adults aged 17 years and above who live within 200 km of Bauchi with advanced glaucoma where the examining ophthalmologist recommends surgery or laser. After obtaining written informed consent, participants will be randomly allocated to MIG plus standard care, or standard care alone. Motivational interviewing will be delivered in Hausa or English by one of two MIG trained personnel. One hundred and fifty participants will be recruited to each arm. The primary outcome is the proportion of participants undergoing laser or surgery within two months of the date given to re attend for the procedure. MIG quality will be assessed using the validated MI treatment integrity scale.

**Discussion:**

Motivational interviewing may be an important tool to increase the acceptance of treatment for glaucoma. The approach is potentially scalable and may be useful for other chronic conditions in Africa.

**Trial registration:**

ISRCTN79330571 (Controlled-Trials.com).

## Background

Glaucoma, a chronic eye disease of unknown cause, is responsible for irreversible blindness in roughly 8.4 million people worldwide
[1]. In Nigeria, the prevalence of blindness in those aged ≥40 years is 4.2% with 16.3% being due to glaucoma
[2]. Glaucoma causes painless, progressive loss of the peripheral field of vision leading to total, irreversible blindness
[3]. Primary open angle glaucoma (POAG), which is the most common type in Africa
[4], is asymptomatic in the early stages
[5]. In Africa, patients with glaucoma present very late, usually with a very advanced stage of the disease
[6-11]. In an earlier unpublished study ([name], Stage at presentation of primary open angle glaucoma in Northern Nigeria) in the same clinic in Bauchi, 75% of the eyes of new glaucoma patients were already blind.

The aim of treatment in glaucoma is to lower the intraocular pressure (IOP), which slows or halts progression
[12]. Treatments are daily eye drops, surgery or laser. Surgery and laser are one-off procedures, and laser can be repeated. Both have acceptably high rates of success. Eye drops (used daily for life) are not recommended in Africa except for educated people who live near eye units, as adherence in other groups is very low. Surgery is the recommended treatment for glaucoma in Africa
[13-16]. However, acceptance of surgery can also be extremely poor. In the earlier unpublished study carried out two years before the trial was planned, fewer than 5% of people offered surgery (trabeculectomy) returned for the procedure. Laser treatment was not available at that time. To prevent glaucoma blindness it is therefore necessary to improve acceptance and adherence to treatment using approaches that are acceptable, replicable and cost-effective in the African setting.

### Motivational interviewing

A review of the literature on approaches to improve adherence to treatment of any kind, and findings from qualitative research in Bauchi were used to modify a form of counseling, called motivational interviewing (MI)
[17]. Motivational interviewing is designed to strengthen personal motivation for and commitment to a specific goal by eliciting and exploring the person’s own reasons for change within an atmosphere of acceptance and compassion. It has shown promise in psychiatry, substance abuse, and healthy life style changes and is being increasingly used in other fields of medical and health care
[18-20]. It is an approach that can be taught at most levels
[21,22], although it is complex to learn and training workshops alone are insufficient. We have named this modified form of MI as MI modified for glaucoma (MIG) for the purpose of this study.

A Cochrane review of interventions for improving adherence to eye drops for glaucoma did not find evidence to support any particular method
[23]. None of the studies included in the review were undertaken in Africa and there is no review of acceptance of surgery or laser treatment. Other Cochrane reviews show the effectiveness of MI for other conditions
[24,25].

To our knowledge this will be the first trial of this nature to be undertaken in Africa. Similar studies in the United Kingdom and United States have only assessed adherence to medical treatment
[26,27].

There is a need for a strategy that is both feasible and effective in increasing awareness about the disease and its management, and the benefits of treatment, to improve acceptance. MIG is a relatively inexpensive technology and local people can be trained to deliver it in the local language. The pilot study described below demonstrated that MIG is acceptable to patients who are not literate and who have no or little knowledge of glaucoma. We acknowledge that there are difficulties in learning and applying this complex approach in the resource-constrained situation in Nigeria, where exposure to counselling of any type is unusual, and where a high proportion of the population have not received any formal education. Bearing this in mind, the two interviewers who will deliver the intervention come from the same community as study participants and are familiar with local social constructs, customs, beliefs and communication patterns, and are also bilingual in English and the predominant local language, Hausa.

The quality of counselling is important in all studies of this type. The Working Alliance Inventory questionnaire (WAI)
[28] has been developed to assess the perceptions of both the counsellor and the participant. In this trial, WAI questionnaires will be completed immediately after the MIG session and analyzed as in other studies
[29,30]. Recorded interviews will also be assessed for fidelity by independent experts, using the motivational interviewing treatment integrity (MITI) scale, a validated tool used for the fidelity testing of MI
[31].

### Pilot study October 2012 to March 2103

The purpose of the pilot study was to assess the acceptability and quality of MIG in adults with advanced glaucoma, to refine the study protocol and finalize data forms, to provide data for the sample size calculation, to refine recruitment and randomization processes and to estimate recruitment rates. The primary outcome was acceptance of laser or surgery on the date given, which was around one month after the date of diagnosis, recruitment and randomization.

### Findings of the pilot study

All those eligible to be included in the pilot study agreed to take part, approximately 20 eligible patients were recruited each month, and the method of randomization using random numbers in sealed envelopes gave equal numbers allocated to MIG or no MIG. All who were offered a MIG interview accepted, and interviews took 20 to 30 minutes per session. None of those offered a second session returned and some participants preferred to have a relative or companion with them. None found the process distressing and reviewing the transcripts showed the quality of the MIG sessions to be satisfactory, but with room for improvement. Data on the primary outcome were available on 45 participants (Table 
1). Nine of the nineteen (47%) participants who had undergone MIG underwent treatment compared with nine of the twenty six participants (35%) who had not undergone MIG. MIG therefore increased treatment rates by 12%. Overall acceptance was 40%, and 75% of these participants underwent laser treatment over surgery. No participants attended for surgery after the date given.

**Table 1 T1:** Pilot study

		**Had surgery**			
		**Yes**	**No**		
**MIG**	Yes	9	10	19	47.4%
	No	9	17	26	34.6%
		18	27	45	

MIG, motivational interviewing modified for glaucoma.

We concluded that MIG is acceptable and the time interval for the primary outcome can be reduced from acceptance within four months of the date given for surgery or laser treatment, to acceptance within two months, as all those accepting treatment did so on the date given and none returned at a later date. Laser treatment is deemed to be more acceptable than surgery.

## Methods/Design

The primary hypothesis is that MI, locally adapted for glaucoma and its treatment (MIG), increases the uptake of treatment amongst individuals with advanced glaucoma in Bauchi State, Nigeria.

A randomized controlled trial with 1:1 allocation to intervention or no intervention will be used to test this hypothesis.

### Study setting

This is a single centre trial, taking place at Abubakar Tafawa Balewa University Teaching Hospital (ABUTH), Bauchi, Bauchi State, Nigeria. [name] is the senior ophthalmologist. The eye department is new and has recently been re-equipped and additional staff appointed.

### Participant eligibility

#### Inclusion criteria

Inclusion criteria for the trial are as follows: must be aged 17 years or above, have a confirmed diagnosis of POAG, have surgery or laser agreed to be the best option for further treatment, are able to understand Hausa or English, and must live within 200 km of the clinic.

#### Exclusion criteria

Exclusion criteria for the study are as follows: patient does not consent, there are other ocular morbidities, any diagnosed systemic diseases that contraindicate surgery or laser, communication problems (such as profound deafness), previous eye surgery (except cataract surgery), or have been referred to Abubakar Tafawa Balewa University Teaching Hospital (ATBUTH) specifically for glaucoma surgery.

### Identification of potential participants and recruitment

Potential participants will be those with POAG where the examining ophthalmologist recommends surgical treatment (trabeculectomy with or without anti-scarring agents) or laser (diode laser trans-scleral cycloablation treatment of the ciliary body which is being increasingly used for advanced glaucoma)
[32,33]. Patients with POAG will be identified by screening everyone aged 17 years and above who attends the outpatient department, regardless of their presenting complaint(s) (Additional file
1). Standard clinical procedures will be used to detect people who the ophthalmic nurse or optometrists suspect as having glaucoma, who will then be examined by an ophthalmologist to confirm the diagnosis. Criteria for referral to the ophthalmologist are one or more of the following:

A cup disc ratio of 0.7 or more in one or both eyes. Optic discs will be assessed in all patients by direct ophthalmoscopy through undilated pupils in a dark room. If the disc is not visible, the Van Herrick’s test will be carried out to exclude narrow angles. The pupils will be dilated and optic discs examined at the slit lamp using a +60D lens; Cup disc ratio difference of 0.2 or more between the two eyes. Examination as before. The cup disc ratio of the two eyes will be compared to detect differences of 0.2 or more; Positive family history of glaucoma regardless of the eye findings. In the Rotterdam study there was a 9.2 relative risk for individuals with a family history of glaucoma
[34]. In the Tasmania study the odds ratio of having a positive family history of POAG was 4.1
[35]. A person has a 20% risk if a parent has the disease, increasing to 50% for a sibling; IOP greater than 26 mmHg in the absence of a view of the discs, even after dilated examination, measured by Goldman application tonometry using standard techniques; Relative apparent pupillary defect (RAPD) assessed in a darkened room using the swinging flash light test
[36]; and high myopia or history of distance spectacle use because of the association with glaucoma
[37].

Everyone suspected of having glaucoma will be referred to the ophthalmologist (usually [name], but other ophthalmologists will also be trained to detect those who are eligible) for a detailed routine ophthalmic examination. The ophthalmologist will confirm the diagnosis of POAG and determine the treatment of choice based the clinical findings (severity) and socio-economic factors likely to influence adherence to medical treatment (such as education and distance from the hospital). Long-term eye drops will be recommended for those who live near the hospital, are educated and can afford topical medication. These individuals will not be eligible for recruitment. Surgery or laser treatment will be recommended for those with an advanced stage of the disease where this offers the best hope for preventing blindness. These individuals will be potential participants. The ophthalmologist will then explain the disease, the treatment options, and the purpose of treatment, as is standard of care. Participants will choose whether to have laser treatment or surgery. The ophthalmologist will then prescribe eye drops and explain how they are to be used whilst waiting for surgery or laser treatment. Everyone offered surgery or laser treatment will be given a date within one month to re-attend for the procedure. Their name and hospital registration number will be written in the surgical register. They will then be escorted to the project manager for recruitment. Participants wishing to change their date of treatment will be offered a new date, and the surgical register, data record form and spreadsheet will be updated.

The eligibility of each potential participant will be checked by the project manager. All those eligible will be recruited after obtaining written informed consent. If the patient does not consent, reasons will be sought and recorded. After obtaining consent a unique identifier number will be issued. All those recruited will be given a red ID card which contains their name, hospital number and study ID. They will be required to present this card at the registration desk at every visit.

### Randomization

The randomization list was generated in Excel, using the *rand between* function by [name], away from the project site. Block randomization with a variable block size was used to ensure that the groups will be balanced over time, as the uptake of laser treatment or surgery may fluctuate over time.

The option of MIG or no MIG was printed on headed paper which was signed and stamped. Each was placed in sequentially-numbered opaque envelopes according to the randomization schedule. Each envelope was sealed and stamped. The same was done for randomization to interviewer A or B. These procedures were undertaken in London by persons not involved in the trial.

For each participant, the interviewer in Bauchi will take the next envelope in the sequence and open it to see whether the patient is allocated to MIG or not. They will write the sequence number on the participant’s form and their unique ID number on the outside of the envelope. After returning the letter to the envelope, the envelope will be kept in a sealed, locked container. The same process will be followed for allocation to interviewer A or B.

All participants, whether randomized to MIG or not, will be given an educational graphic leaflet called ‘Silent Thief’ (Additional file
2). All participants will, therefore, receive some additional information about glaucoma and its management.

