### Ascertainment of outcomes

#### Primary outcome

All data on socioeconomic variables, clinical findings and the date given for surgery will be entered into a customized database on the day of recruitment. Software will be used to generate a spreadsheet which will be constantly updated. The spreadsheet will have the patient’s unique ID, name, sex, hospital number, detailed address, contact phone number, the date given for surgery (or the revised date, if relevant), the date the patient came for surgery and the ‘tracing date’ (date two months after the date given for surgery). The spreadsheet will not contain the randomization sequence number to maintain blinding. The software will be programmed to indicate the date two months after the date booked for laser treatment or surgery (or the revised date). This is the ‘tracing date’ when participants will be traced (see below). Every surgery day the spreadsheet will be reviewed to identify participants who should attend for surgery or laser treatment that day. The surgical register will be checked to see who did and who did not attend on the appointed operation day. The data recording form will be completed. The data will be entered into the database so that the spreadsheet can be updated.

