### Before and after recruitment at T0

Data will be collected for name, age, gender, clinical findings and date given to attend for surgery or laser treatment. For those who refuse, reasons for not agreeing to participate will be sought. For those who agree, contact details will be recorded: detailed address; telephone numbers of individual/family/neighbor; sociodemographic data and randomization sequence number. All data will be entered into a customized, password protected database on the day of recruitment. The form will be kept in a lockable cupboard only accessible to the project manager in an office dedicated to the trial, which is locked when not in use.

For those allocated to MIG the interview will be conducted at T0. If a second MI session is indicated, the reason for this will be recorded. After every interview, WAI questionnaires will be completed independently by the participant and the interviewer. These forms will be kept in a lockable cupboard in a separate office dedicated to the MIG interviews. This office will be locked at all times when not in use for MIG sessions. The project manager and ophthalmologist will not have access to these forms at any time. Data from these forms will be entered into a separate password protected database.

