### Data management

#### Data entry

Databases have been created in Epidata and Access, with range and consistency checks. Data will be double entered by the project manager, who has been trained in data entry. Data will be entered as soon as possible after recruitment, so that the ‘surgery date’ and ‘tracing date’ outputs can be generated (as above). Random checks of the quality of data entry will be undertaken by [name] on a regular basis. Frequency distributions will be explored and data of outliers checked for accuracy.

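### The allocation envelope is opened by the MIG interviewer before the participant's ID goes on it, and the sequence number reaches the project manager who is meant to be blinded: two small, avoidable weaknesses

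*Protocol article*

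**What the plan says.** **Opening the envelope.** The Randomization section says the interviewer will "take the next envelope in the sequence and open it to see whether the patient is allocated to MIG or not". The next sentence reads "They will write the sequence number on the participant’s form and their unique ID number on the outside of the envelope". The used envelope then goes into locked storage, and the same steps apply to a second envelope that assigns interviewer A or B. The Motivational interviewing section identifies the interviewers as those "who deliver" MIG in substance: "the two interviewers who will deliver the intervention come from the same community as study participants".

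**The sequence number.** The Blinding section states that the project manager and the study ophthalmologist, who obtain and check primary outcome data, are blinded. Under Ascertainment of outcomes (Primary outcome): "The spreadsheet will not contain the randomization sequence number to maintain blinding". The section on data before and after recruitment at T0, however, lists "sociodemographic data and randomization sequence number" among the items recorded, sends all data to the database on the day of recruitment, and keeps the form in a cupboard that only the project manager can open. Data entry adds: "Data will be double entered by the project manager".

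**The concern.** Two separate protections are involved.

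The first is the integrity of allocation after consent. In the order written, the person who delivers the intervention learns the allocation first and records whose it is second. The primary outcome is whether a person comes back for laser or surgery, which depends heavily on willingness. If an opened envelope were given to a different waiting participant because one seemed more receptive, the comparison would be biased in favour of MIG.

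The second is blinding of outcome ascertainment. The article itself treats the sequence number as something to keep away from outcome tracing, yet routes it to a person who carries out that tracing. The outcome is fairly objective, but it leaves some room for judgement. The two-month window runs from the booked or revised date, and later contact with non-attenders asks whether they attended unnoticed or were treated elsewhere.

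**Working it through.** The plan attaches no figure to this point, and the sample size calculation is not affected. The check is of sequence and routing.

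**1. Order of steps at allocation**

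| Step | Who | Where stated |
|---|---|---|
| Eligibility check, consent, study ID issued | Project manager checks and takes consent; ID follows consent | Identification of potential participants and recruitment; Consent |
| Next envelope taken and opened | Interviewer | Randomization |
| Sequence number written on form, ID on envelope | Interviewer | Randomization |
| Envelope locked away | Key holder not named | Randomization |

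The ID exists before the envelope is opened, so it could be written on the sealed envelope. The described order does not do so.

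**2. How often could an exchange arise?** An exchange needs two consented but unallocated participants at the same time. Holding an opened envelope for someone who arrives later would put envelope order out of step with ID order. From Trial status, 70 participants were recruited from 2 September 2013 to the end of January 2014, five months: 70 / 5 = 14 a month. Clinic days are not stated. Assuming five recruiting days a week, there are 5 × 52 / 12 = 21.7 days a month, and 14 / 21.7 = 0.65 participants a day. Assuming recruitment on only one day a week, there are 52 / 12 = 4.33 days a month, and 14 / 4.33 = 3.2 a day. Two waiting together is therefore probably infrequent if recruitment is spread over the week, and less so if it is concentrated.

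**3. Route of the sequence number.** It goes from the envelope to the participant's form (Randomization), which only the project manager can reach (T0 data). It is listed among the T0 data, all of which go to the database (T0 data), where the project manager enters them (Data entry). The project manager is also one of the two people named in the Blinding section. The exclusion under Ascertainment of outcomes covers the spreadsheet only.

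**4. Does the number reveal the arm?** Block size varies, the list was generated away from the site, the envelopes are opaque, and used ones are locked away. Without the list or the envelopes, the number does not give the allocation.

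**5. Why no size is given.** One can assume no true effect, 35% uptake and 150 per arm (35% × 150 = 52.5 acceptors), and exchange *s* control-bound acceptors for *s* MIG-bound non-acceptors. The rates become (52.5 + *s*)/150 and (52.5 − *s*)/150. For *s* = 2 this is 36.3% against 33.7%, risk ratio 1.08. For *s* = 10 it is 41.7% against 28.3%, risk ratio 1.47. The result is fixed by the chosen *s* and by the assumption that acceptors are predicted perfectly. The article supports neither.

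**The case against.** It can fairly be said that the envelope is drawn for a known participant who has already consented and holds an ID. Reading a fixed procedure into the sentence order of a condensed article may be too literal. The envelopes are numbered, opaque, sealed and prepared off site. The interviewer would have to judge willingness before any MIG session. The outcome is checked against a surgical register that carries no study ID, and the forms that would show who had MIG are kept where the project manager cannot reach them. Taken literally, excluding the number from the spreadsheet does not conflict with having it in the database.

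Most of this stands, and it rules out several stronger readings:

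- A reader might infer that an envelope could be reassigned without trace. The documents do not support that: numbered envelopes, a number on the form, an ID on the envelope and same-day data entry leave some trail.
- A reader might infer selective enrolment. Eligibility, consent and ID come before the envelope in the written order.
- A reader might infer that the project manager is unblinded. The number alone does not show the arm.
- A reader might infer that a second number, from the interviewer A or B envelope, identifies MIG participants. That would follow only if controls draw no such envelope, which the text does not say. The T0 list mentions a single sequence number, and the flow chart and data forms that might settle it are not shown.
- A reader might attach a percentage bias. Any such figure comes from assumed inputs.

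What this does not answer is narrower. The stated order is open first and label second, by the person who delivers the intervention. The stated reason for keeping the number off the spreadsheet also applies to the form and database that the same person handles.

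**Conclusion.** The point holds as a cheap improvement to a stated procedure. Labelling after opening leaves an avoidable and probably infrequent chance to reassign an envelope between consented participants. Recording the sequence number on the project manager's form and among the data the project manager enters is at odds with the purpose of the spreadsheet precaution and with the Blinding section. Blinding is weakened, not shown to be broken, and nothing suggests misconduct. No bias magnitude can be derived. The judgement that opportunities are infrequent assumes that recruitment is spread across the week at the reported rate.

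**What to change.** For participants still to be randomized (300 − 70 = 230 at the date of Trial status):

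1. Write the study ID, date and time on the sealed envelope and in a sequential log before the envelope is opened.
2. Keep the sequence number, and any interviewer A or B envelope number, off the project manager's form and database. Hold them in a separate restricted record and link by study ID at analysis. The separate office and database already used for the WAI forms offer a model.
3. Have someone other than the interviewers and the project manager check the log against the order of consent and ID issue. This replaces the cross-check lost when the number leaves the project manager's database.
4. Align the Randomization, T0 data collection and Data entry text with the Blinding section and the spreadsheet precaution.

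The cost is a log sheet, a periodic check and one linkage step. The sample size and the analysis do not change.
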